# 3. STUDY DESIGN

## 3.1 Intervention study

This study is a single-blind cross-over intervention (challenge) study, planned to run from the end of October till half December 2009.

In this study obese type 2 diabetic subjects will be studied and compared to age and BMI matched healthy obese controls and to age-matched healthy lean controls.

A total of 22 type 2 diabetic obese men, 22 obese men and 22 lean men will consume high-fat milkshakes containing 95 g of fat, mainly consisting of either SFA, MUFA or PUFA. No differences can be seen or tasted between the shakes.

The 22 type 2 diabetic obese, 22 obese and 22 lean men will be randomly divided in 6 groups to determine in which order they will receive the milkshakes. The groups will receive a different high-fat shake every two weeks (see table 1). There will be a minimal period of one week between two testing days, in order to exclude carry over effects. Six persons will be evaluated on each testing day.

Table1: Experimental study design

|  |  | Week 1/2 | Week 3/4 | Week 5/6 |
| --- | --- | --- | --- | --- |
| Intervention order | Group 1 | SFA | MUFA | PUFA |
| Group 2 | SFA | PUFA | MUFA |
| Group 3 | MUFA | SFA | PUFA |
| Group 4 | MUFA | PUFA | SFA |
| Group 5 | PUFA | SFA | MUFA |
| Group 6 | PUFA | MUFA | SFA |

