# STATISTICAL ANALYSIS

In this cross-over study, each subject will consume the three shakes and can be used as its own reference.

Analysis of PBMC whole genome expression data will be performed using a Bayesian linear regression model (implemented in the software package LIMMA; [www.bioconductor.org](http://www.bioconductor.org/)). Raw microarray data will be normalized using RMA quantile normalization. Statistically significant changed genes will be identified by student paired t-test followed by a false discovery rate correction (FDR) The latter is used to correct for multiple testing.

Analysis of secondary and tertiary outcome variables (endothelial function, glucose etc.) will be in SPSS version 15.0. Effects of treatment (SFA, MUFA, PUFA) within each risk group (lean healthy, obese, type 2 diabetic) will be tested by repeated measures ANOVA (mixed model) using pre-defined contrasts, i.e. 2 versus 0 hrs and 4 versus 2 hrs. Additionally, incremental areas under the curve will be calculated for all significant altered outcome variables using the trapezoïdal rule and compared between treatments using one-way ANOVA.

Differences between risk groups for each treatment will be tested by one-way ANOVA followed by LSD correction. Additionally, incremental areas under the curve will be calculated for all significant altered outcome variables and compared between risk groups using one-way ANOVA.

An empty ANOVA table providing more information about the analysis is included below.

| Variable | df |
| --- | --- |
| Risk profile (diabetic, obese, control) | 2 |
| Treatment (SFA, MUFA, PUFA) | 2 |
| Time (0,2,4) | 2 |
| Interaction | 8 |
| Error | 579 |

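### The section 8 ANOVA table has no term for men: its single 579-df error line fits neither analysis described in the text and, if used, would inflate false positives for risk profile in secondary and tertiary outcomes

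*Protocol*

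**What the plan says.** Section 8 stresses the cross-over structure: "each subject will consume the three shakes and can be used as its own reference". For secondary and tertiary outcomes it then names two kinds of analysis.

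- Shake effects, within each risk group, "will be tested by repeated measures ANOVA (mixed model"), with contrasts between time points.
- Differences between risk groups, separately for each shake, by one-way ANOVA with LSD, and again by one-way ANOVA on incremental areas under the curve (iAUC).

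The section closes its description with "An empty ANOVA table providing more information about the analysis is included below". The rows are "Risk profile (diabetic, obese, control) | 2", "Treatment (SFA, MUFA, PUFA) | 2", time with 2 df, "Interaction | 8", and one error row with 579 df. There is no row for men and no second error line.

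The primary outcome, PBMC gene expression, has its own analysis in the same section (LIMMA, paired t-tests, false discovery rate).

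**The concern.** Risk profile belongs to the man and does not change between his nine measurements. There are 66 independent units for comparing the three groups, so the natural error is the variation between men within a group, on 66 − 3 = 63 df. A single error line mixes that variation with the smaller variation within men and judges everything against the blend. For risk profile the blend is too small, so stable differences between men can pass for group effects. For shakes and times it is too large, which gives away the precision that a cross-over is meant to provide.

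The table is also the only place in the protocol where risk profile, treatment, time and an interaction stand in one model. Research questions 2 and 3 in section 2.1 ask whether changes in inflammatory response and endothelial function differ between risk groups. An analyst looking for a joint model would find only this one.

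**Working it through.** **Inputs from the protocol.** Section 3.1: "A total of 22 type 2 diabetic obese men, 22 obese men and 22 lean men will consume high-fat milkshakes", so 66 men. Three shakes per man (section 8). Three times, 0, 2 and 4 h (section 8 table). Measurements: 66 × 3 × 3 = 594, nine per man. Section 4.1 gives twenty diabetic men instead of 22; 64 men would give 64 × 9 − 1 − 14 = 561 error df, so the table was built on 22 per group.

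**Reproducing the plan's figure.** 594 − 1 − (2 + 2 + 2 + 8) = 593 − 14 = 579, exactly. No df are removed for men.

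**What a full partition gives.** Between men: 65 df = 2 (risk profile) + 63 (men within risk profile). Within men: 66 × 8 = 528 df. With the table's own terms, 528 − 2 − 2 − 8 = 516 remain as within-man error, and 516 + 63 = 579. The 8-df interaction is 2 × 2 × 2, the three-way term alone. The three two-way interactions, 4 + 4 + 4 = 12 df, have no row. With them the within-man error is 516 − 12 = 504.

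**Assumptions.** The protocol gives neither a significance level nor a within-man correlation ρ. I take 5%, compound symmetry, and a range of ρ. With total variance 1 and no true effects:

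- risk-profile sum of squares ~ (1 + 8ρ) χ²(2)
- men within risk profile ~ (1 + 8ρ) χ²(63)
- within-man residual ~ (1 − ρ) χ²(516)
- treatment (likewise time) ~ (1 − ρ) χ²(2)

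The table's test divides by the pooled mean square, (between + within)/579, and compares with F(0.95; 2, 579) = 3.011. The correct risk-profile test divides by the between-man mean square and uses F(0.95; 2, 63) = 3.143.

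**Results** (400,000 simulated draws per ρ):

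| ρ (assumed) | Risk profile on 579 df | Risk profile on 63 df | Treatment on 579 df |
|---|---|---|---|
| 0 | 4.9% | 4.9% | 5.0% |
| 0.05 | 11.7% | 5.0% | 4.3% |
| 0.1 | 18.9% | 5.0% | 3.6% |
| 0.2 | 31.8% | 5.1% | 2.4% |
| 0.5 | 55.3% | 5.0% | 0.3% |
| 0.7 | 63.9% | 5.0% | 0.01% |
| 0.9 | 69.8% | 5.0% | below 0.01% |

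**Hand check at ρ = 0.2.** Expected pooled mean square = (63 × 2.6 + 516 × 0.8)/579 = 576.6/579 = 0.996. Treating it as fixed, the risk-profile rate is exp(−3.011 × 0.996/2.6) ≈ 0.32, and the treatment rate is exp(−3.011 × 0.996/0.8) ≈ 0.024. Both agree with the simulation.

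**The one-way ANOVA in the text.** With one value per man (one time point, a change or an iAUC) it has 2 and 63 df and holds 5%. The text does not say how the three times enter. If they were pooled, the error would have 66 × 3 − 3 = 195 df, and the rate would be about 12% at ρ = 0.2, 23% at 0.5 and 32% at 0.8.

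**The case against.** The strongest reply is that the table is not the risk-group test. The text assigns that comparison to one-way ANOVA for each shake and on iAUC, which is valid with one value per man, and it tests shakes by repeated measures. The table is described only as extra information. This stands: a reader might infer that between 30% and 70% of null outcomes will be declared different between risk groups, but the protocol does not commit to testing them on this line. That range also needs a correlation of roughly 0.19 to 0.9, which the protocol does not give.

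A reader might also infer that no model with a subject term could show 579. That is wrong. A random intercept uses no fixed-effect df, so residual df are 594 − 15 = 579. If the between-man variance were used correctly and only the df were wrong, the false-positive rate would be P(F(2, 63) > 3.011) = (1 + 2 × 3.011/63)^(−31.5) ≈ 5.6%. The inflation comes from the pooled error mean square, not from the number 579 itself. A single error row in a classical ANOVA table is still most naturally read as a pooled error.

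Third, the questions about whether changes differ by group are interactions with time. For those a pooled error is conservative under compound symmetry. Only the risk-profile main effect is anticonservative.

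These replies limit the consequence. They do not explain the table, which has no row for men, omits the two-way interactions, and corresponds to neither analysis in the text.

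**Conclusion.** The table is wrong as printed, read as a single-error ANOVA, and must be reconciled with its own section. If it were used, the risk-profile main effect would have a false-positive rate of about 12–19% at a correlation of 0.05–0.1, rising to about 70% at 0.9, instead of 5%. Treatment and time tests would reject too rarely. These sizes rest on an assumed 5% level, an assumed correlation, compound symmetry and all 66 men completing.

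The scope is secondary and tertiary outcomes. The primary gene-expression analysis does not use this table. The documents support a conditional statement about what the table would do, not a prediction that false group differences will be reported.

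**What to change.** Replace the table with one that separates the strata.

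- **Between men:** risk profile (2 df), tested against men within risk profile (63 df).
- **Within men:** treatment (2), time (2), the three two-way interactions (4 + 4 + 4) and the three-way interaction (8), each tested against its within-man error. These errors total 504 df, for example 126 for treatment by man, 126 for time by man and 252 for treatment by time by man.

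Alternatively, state one mixed model with these fixed effects, random intercepts for man and for man-by-test-day, and Satterthwaite df, and drop the 579.

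In either case, add that the one-way ANOVAs between risk groups use one value per man (a single time point, a change or an iAUC), so that table and text agree.

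The cost is a rewrite of section 8, with no new data and no more men. Risk-profile p-values would be larger only if the table would otherwise have been used.

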## 6.2 Randomisation and blinding

Before the start of the study, participants of each ‘risk profile group’ will be randomly allocated to one of the six intervention groups (see table 1). The shakes will be labeled with three different codes. Participants will not know which code is allocated to which shake.

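### The printed ANOVA table fits neither study period nor subject, although 22 men per risk group cannot be balanced over six shake orders; the bias is modest and adding both terms costs almost nothing.

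*Protocol*

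**What the plan says.** Section 3.1 gives each man three shakes in three two-week windows. It states that "22 obese and 22 lean men will be randomly divided in 6 groups to determine in which order they will receive the milkshakes", and treats the 22 diabetic men in the same way. Section 6.2 (Randomisation and blinding) says only that participants of each risk group "will be randomly allocated to one of the six intervention groups"; it gives no block size or quota. Section 4.5 plans for 20 completers per group.

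For the secondary and tertiary outcomes, the statistical analysis section says "Effects of treatment (SFA, MUFA, PUFA) within each risk group (lean healthy, obese, type 2 diabetic) will be tested by repeated measures ANOVA", with 2 versus 0 h and 4 versus 2 h as pre-defined contrasts and incremental areas under the curve in addition. It then prints the model: "An empty ANOVA table providing more information about the analysis is included below". The table lists risk profile (2), treatment (2), time at 0, 2 and 4 hours (2), interaction (8) and error (579).

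For the primary outcome, "Analysis of PBMC whole genome expression data will be performed using a Bayesian linear regression model" in LIMMA, without a list of terms, and "Statistically significant changed genes will be identified by student paired t-test followed by a false discovery rate correction". The protocol does not say what forms a pair.

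**The concern.** In a three-period cross-over, whatever differs between visits apart from the shake is a period effect. It drops out of a shake comparison only if each shake is given equally often in each period or if period is in the model. Here the first condition cannot be met within a risk group, and the printed table does not meet the second. Its time line is hours within a study day, not study period.

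Some drift over visits is plausible. The study is "planned to run from the end of October till half December 2009", and the Summary gives 172 ml of blood per visit, so 2 × 172 = 344 ml has been drawn before the third visit. At stake are a distortion of the within-group shake contrasts that depends on the allocation realised, and period variation left in the error.

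**Working it through.** **1. The plan's own figure.** 66 men × 3 shakes × 3 hours − 1 = 593. The listed effects use 2 + 2 + 2 + 8 = 14, and 593 − 14 = 579, exactly the printed error df. Period would take 2 more and subject within risk group 66 − 3 = 63 more. The figure 579 arises only with both left out.

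**2. Balance.** Equal use of each shake in each period needs n/3 men per cell: 22/3 = 7.33 and 20/3 = 6.67. Neither is whole, so no allocation of 22 or 20 men achieves it.

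**3. Share of a shift that leaks.** With no period term, a unit shift in period p enters the contrast of shakes a and b with weight (n_ap − n_bp)/n, where n_ap is the number of men on shake a in period p.

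- Orders filled 4,4,4,3,3,4 (in the sequence of Table 1): the cells hold 7 or 8 men, so the worst weight is 1/22 = 4.5%.
- Orders filled 3,3,4,4,4,4: in weeks 1/2 there are 6 men on SFA and 8 each on MUFA and PUFA, so the weight is 2/22 = 9.1%.
- All 15 near-equal splits (four orders of 4, two of 3) give one of these two values. No allocation of 22 men does better than 1/22. With 20 men the minimum is 1/20 = 5%, and near-equal splits reach 10%.
- Simple randomisation, with the count per shake in a period multinomial (22; 1/3, 1/3, 1/3): the worst of the three contrasts has median 4/22 = 18% and 95th percentile 9/22 = 41%. One named contrast has 3/22 = 14% and 7/22 = 32%.

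**4. Which comparisons are affected.** If a shift d raises all of a day's values equally, then (y2 + d) − (y0 + d) = y2 − y0. The 2 versus 0 h and 4 versus 2 h contrasts and the incremental area lose it under every allocation. It stays in the treatment line of the table, which averages over the hours, and in any shake comparison at one hour or at fasting. If the response itself changes by d between periods, the weights in step 3 apply to comparisons of changes as well.

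**5. Size, for assumed shifts.** The within-man SD and the size of any shift are not in the protocol. With one value per visit and 22 men, the SE of a shake contrast is √(2/22) = 0.30 within-man SD. A 0.5 SD shift in one period gives:

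| Allocation | Bias (SD) |
|---|---|
| Near-equal, worst | 0.5 × 2/22 = 0.045 |
| Simple randomisation, median of worst contrast | 0.5 × 4/22 = 0.09 |

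**6. Precision.** With roughly balanced orders, a shift of d SD in one period adds d, −d or 0 to a man's paired difference with probability 1/3 each. The variance rises by a factor 1 + d²/3: 8% for d = 0.5 and 33% for d = 1.

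**7. Error rate.** Paired tests of shake against shake were simulated (20,000 trials per setting) with no shake effect and a 1 SD first-period shift. Near-equal splits gave a type I error of 2–4% where the shift reached the comparison, because the unmodelled variation makes the test conservative. A lopsided split (7,6,2,2,3,2) gave a bias of 0.41 SD and a type I error of 17% on levels. It gave 12% on changes when the response itself shifted. A pure level shift left the test on changes at 5% throughout.

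**The case against.** The strongest defence is that the planned analysis already removes most of the problem. The pre-defined contrasts and the incremental areas are changes within one study day, so a level shift cancels. That stands and confines the point to the treatment line, to single-time or fasting comparisons, and to a drift in the response, which the protocol gives no reason to expect.

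Secondly, a table that also omits subject contradicts the text, which calls for a repeated-measures mixed model and uses each man as his own reference. The table may be only a sketch. That is fair, but it is the only statement of the model's terms, and it is a stated choice rather than a detail left for later.

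Thirdly, the larger leak figures assume simple randomisation. Dividing men into six groups fits near-equal groups at least as well, and then the leak is at most 9.1%. This stands. Over repeated randomisations the leak averages zero, but the trial analyses one realised allocation.

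Lastly, section 6.3.4 postpones any visit with Hb below 8.4 mmol/L, which limits drift from blood loss.

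A reader might infer that the primary gene analysis is biased because a paired t-test has no period term. The documents do not support that. The pairs are undefined, the reference to changed genes points to after versus before on the same day, where a level shift cancels, and the LIMMA model could include period.

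**Conclusion.** The point holds in limited form and is a minor improvement. The printed model leaves out period and subject, and the within-group shake contrasts cannot be balanced. With near-equal orders the worst contrast takes 4.5–9.1% of a one-period shift; under simple randomisation the median is 18% and the 95th percentile 41%. For an assumed 0.5 SD shift the bias is 0.045–0.09 SD (near-equal worst to simple-randomisation median) against an SE of 0.30 SD, plus some lost precision. This assumes a shift that is additive and common to the men in a period; the protocol does not show that one exists.

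Two stronger readings are not supported. One is that carry-over biases the PUFA contrasts, because the protocol relies on a gap: "There will be a minimal period of one week between two testing days, in order to exclude carry over effects". Its size is unknown and may be zero, and a week is only the minimum in a two-week schedule. The other is that the leak carries into the planned comparison of risk groups as a difference of shake differences. The protocol compares risk groups separately for each shake, by one-way ANOVA.

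**What to change.** Add period (2 df), with subject as block, to the model for the secondary and tertiary outcomes, and to the LIMMA model wherever shakes are compared with each other. This removes an additive period shift at any split of orders, including after dropout. It does not remove calendar drift inside a two-week window.

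The cost is in the analysis only.

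- Degrees of freedom: period takes the printed error from 579 to 577, and subject takes it to 577 − 63 = 514. Within one risk group with one value per visit and subject fitted, period takes 42 to 40 (critical t 2.018 to 2.021).
- Variance of a shake contrast from adding period: 0–0.6% more with near-equal orders; under simple randomisation a median of 3.4% and a 95th percentile of about 14–16%.
- Break-even: by the factor 1 + d²/3, period pays for itself in precision once the shift exceeds about √(3 × 0.00625) = 0.14 SD (near-equal) or √(3 × 0.0344) = 0.32 SD (simple, median).

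If allocation is still open, stating blocked randomisation over the six orders within each risk group would keep the split near-equal. A term for PUFA as the immediately preceding shake is at most an optional, coarse sensitivity analysis.

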# ETHICAL CONSIDERATIONS

## 9.1 Regulation statement

The study will be conducted according to the principles of the Declaration of Helsinki (Seoul, 2008) and in accordance with the Medical Research Involving Human Subjects Act (WMO).

## 9.2 Recruitment and consent

Subjects will be recruited from Wageningen and surrounding area. An invitation to participate will be sent by email to all eligible men in the database of participants of past scientific studies in the Division of Human Nutrition. If needed, additional recruitment of subjects will take place by advertisement in the University Weekly (Resource magazine) and local newspapers.

For the recruitment of obese (and diabetic) subjects an advertisement will be placed on the website of the Obesity Association ([www.obesitasvereniging.nl](http://www.obesitasvereniging.nl/)). Obese type 2 diabetic subjects will be informed about the study with the help of general practitioners.

Interested participants will be invited for an information meeting organized 6 weeks before the start of the study where the study, requirements for participation and risks will be explained by the Principal Investigator. An information booklet will be provided during this information meeting. Written informed consent will be obtained during a screening visit 4 weeks before the start of the study. In the informed consent we will ask the participants if they want to give permission for anonymous storage of their blood samples for possible additional analyses in the future. We will ask the METC for approval before performing additional analyses.

## 9.3 Privacy

Personal data will be stored in a closed locker and a password-protected file, to which only the investigators have access. Samples will be coded and destroyed within twelve years. Only the investigators have access to the code.

## 9.4 Benefits and risks assessment, group relatedness

### 9.4.1 Potential value of the research

The outcome of this study will provide us with valuable information about the postprandial response of high risk subjects to different fatty acids.

The collected data of PBMC gene expression, plasma cytokine profiles, endothelial function plasma lipid profile, glucose, insulin and activation markers of white blood cells could provide us knowledge about the molecular mechanisms behind development of postprandial dyslipidemia and endothelial dysfunction and the effect of different fatty acids on this process.

The immune stimulation experiment with LPS will provide us with more information about the immune response in obese and diabetic subjects and the effect of a high fat challenge on this.

### 9.4.2 Benefits for the participants

Participants that complete the study will receive €90. Participants are free to withdraw from further participation for any reason and at any time during the trial and will receive a proportional bonus for the effort they made (30 euro for each completed testing day). Participants can receive a summary of the results with averages of the group after the end of the study. Furthermore, participants will receive a meal the day before each study day and at the end of each study day.

### 9.4.3 Risks for the participants

There are minor risks for the participants during the intervention. The consumption of the high-fat shakes is not expected to be associated with any risk, although in rare cases it could lead to mild gastro-intestinal discomfort (belching, flatulence or loose stools). Participants also could experience a fatty taste in their mouth after intake of the high-fat shakes, and a fishy aftertaste in case of the PUFA enriched shake. Venapunctures can occasionally cause a local haematoma or bruise and some participants may report pain or discomfort.

The performed functional measurements of endothelial function are non-invasive and risks are therefore minimal.

MRI is a safe procedure, with no known health risk as long as no contraindication is met. These contraindications include persons with the following devices:

- Central nervous system aneurysm clips;
- Implanted neural stimulator;
- Implanted cardiac pacemaker or defibrillator;
- Cochlear implant;
- Ocular foreign body (e.g. metal shavings);
- Insulin pump;
- Metal shrapnel or bullet;
- Or metal containing corpora aliena in the eye of brains

MRI can result in a ‘coincidence’ finding. These findings should be reported and subjects will be informed about this.

Subjects that do not want to be informed about a ‘coincidence’ finding can not participate in the MRI measurement.

The time investment requested from the participants is shown in table 4.

Table 4: Time investment per participant

|  | Time at university/ hospital (OGTT, consumption of milkshakes, blood sampling etc) | Questionnaires | Weight/height /blood pressure | Blood collection during screening | Total |
| --- | --- | --- | --- | --- | --- |
| Information meeting | 1 hour |  |  |  | 1 hr |
| Screening | 2 hours | 15 min | 15 min | 10 min | 2.5 hrs |
| Week 1/2 | 4.5 hours |  |  |  | 4.5 hrs |
| Week 3/4 | 4.5 hours |  |  |  | 4.5 hrs |
| Week 5/6 | 4.5 hours |  |  |  | 4.5 hrs |
| MRI | 1 hour |  |  |  | 1 hr |
| Total time whole study | | | | | 18 hrs. |

